Osteoinduction and, as a consequence, osteogenesis are intricately linked to angiogenesis in normal fracture healing [25]. Corticoperiosteal tissue from the medial femoral condyle can provide a vascularized source of tissue rich in osteogenic progenitor cells. Studies have shown that specific osteoprogenitor cells, such as those in periosteal tissue, are stimulated by growth factors to differentiate and form bone [26]. As a result, scaffolds are subject to the uniform delivery of host-derived growth factors, mesenchymal stem cells, and an optimal extra-cellular environment, of which all are essential for bone regeneration.

Investigations into periosteal flaps as sources of axial vascularization are well documented in animal models. Nau et al [22] compared periosteal flaps with a tricalcium phosphate scaffold that did or did not have bone marrow–derived mononuclear cells to a periosteal flap alone. These were used in rat femurs with critical size defects. The periosteal flap with tricalcium phosphate and marrow cells had a significant increase in new bone formation, vascularization and strength radiographic, histological, and biomechanical outcomes at 4 weeks. More recently, Sparks et al [20] combined a pedicled corticoperiosteal flap, which was based on the anterior tibial vessels, with a PCL-TCP scaffold to bridge 3- and 6-cm tibial segmentectomies. The radiological and histological outcomes demonstrated new bone regeneration and excellent scaffold integration, with the complete bridging of both defects at 12 months.

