## Methods

### Study Design

Our study will be a single-arm feasibility trial that evaluates the outcomes of using an mPCL-TCP scaffold, in conjunction with a vascularized corticoperiosteal tissue, in participants with acquired defects of the calvarial bones of the skull resulting from trauma, malignancy, or infection. The study will capture data that will be used to inform the design of future clinical trials in this area.

The mPCL-TCP scaffold that will be used in the study will be manufactured by the trial sponsor—Osteopore International Pte Ltd (Singapore). Osteopore products are made of a US Food and Drug Administration–approved polymer (K051093) called *polycaprolactone*, which is bioabsorbable, is malleable, is slow to degrade, and possesses mechanical strength that is similar to that of trabecular bone. The product will be manufactured by using 3D printing technology that is precise and allows for the customization of shape and geometry. The unique, 3D-printed, biomimetic microarchitecture of the 3D scaffolding, which is contained within Osteopore products, allows for the infiltration of cells and blood vessels, of which both play a key role in wound healing and tissue repair.

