### Sample Size

This feasibility trial will recruit a total of 10 patients.

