### End Points

The key primary end points for evaluation in our single-arm study are the time to the formation of stable, regenerated bone that is sufficient for protecting the brain (ie, radiographic or clinical evidence of bony union) and patient-reported outcomes. These primary end points serve as surrogate markers for satisfactory bone healing but, more importantly, are clinically useful for and relevant to the study goal and overarching purpose of the intervention. Functional outcomes are more difficult to measure reliably and are therefore secondary outcomes, which will be measured with the QOLIBRI and the SF-36 questionnaires [40]. The schedule of assessments is presented in Table 1.

**Table 1 table1:** Schedule of assessments.

			Multidisciplinary team review		Enrollment		Reconstruction		Follow-up period		
									1-month review		3-, 6-, 9-, 12-, 15-, 18-, 21-, and 24-month review
Time point^a^			−t_2_		−t_1_		0		T_1_		T_2-9_

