### Analysis

All patients who are registered for the trial will be accounted for in the (intention-to-treat) analysis. For retrospectively recruited patients, all data points may not be available for all assessments, or data collection may have occurred outside of the trial-specific window (eg, CT data are available for the 9-month follow-up but are not available for the 12-month follow-up). In such cases, these subjects will not be evaluated for a particular analysis unless the number of data points required for the analysis is enough, or a trend can be extrapolated from the data that were collected outside of the trial-specified window.

A quantitative analysis that relates to the evaluation of the cost-effectiveness of this approach will not be undertaken as a part of this study, as the data set will most likely be too small to achieve statistical significance. Instead, the outcome measures that have an impact on the financial burden for treating patients will be combined with data from other similar trials that are conducted in the future, and the analysis of health economics data will be undertaken at that point.

Statistical analyses of descriptive statistics for the demographic, primary, and secondary outcomes at each time point will be conducted. A comparison analysis of the questionnaire results at each time point and a univariate Cox regression analysis of the time to weight-bearing for the affected limbs will be performed due to the small sample size. Statistical significance will be defined as *P*<.05. Data will be analyzed by using SPSS for Windows version 22 (IBM Corporation).

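### The only time-to-event analysis named is a Cox model of time to weight-bearing of affected limbs, which is not an outcome of this skull trial; the primary end point, time to bony union, has only generic descriptive statistics

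*Protocol article*

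**What the plan says.** Study Design describes a single-arm feasibility trial in "participants with acquired defects of the calvarial bones of the skull resulting from trauma, malignancy, or infection". Sample Size states: "This feasibility trial will recruit a total of 10 patients".

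End Points names two primary end points. One is "the time to the formation of stable, regenerated bone that is sufficient for protecting the brain", which the section explains as union shown on imaging or clinically. The other is patient-reported outcomes. On secondary outcomes it says: "Functional outcomes are more difficult to measure reliably and are therefore secondary outcomes, which will be measured with the QOLIBRI and the SF-36 questionnaires".

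Intervention sets the trial imaging for union (CT and/or MRI) at 1, 12 and 24 months after surgery. The two questionnaires are given before reconstruction and at the same three times.

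Analysis names three things:

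- a descriptive summary: "Statistical analyses of descriptive statistics for the demographic, primary, and secondary outcomes at each time point will be conducted";
- a comparison of questionnaire results at each time point;
- "a univariate Cox regression analysis of the time to weight-bearing for the affected limbs will be performed due to the small sample size".

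**The concern.** The third analysis concerns an outcome that the trial does not define. The site under study is the skull, and limb weight-bearing appears nowhere else in the article. Meanwhile a primary end point that is itself a time to an event has no time-to-event method attached to it.

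Taken literally, the sentence commits the analysts to a model for which no outcome is defined and no data collection is specified. It also leaves open how time to union will be estimated and how patients without union at 24 months will enter the summary. The trial is meant to inform the design of later trials, and a clear description of time to union is among the main things it can offer them.

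**Working it through.** The check is one of consistency between sections. The protocol gives no figure on this point to reproduce: the sample size of 10 carries no power, effect size or event count. Its only arithmetic is accrual, and that is consistent (5 per year × 2 years = 10; × 3 years = 15).

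**Step 1. Match each outcome to its definition, schedule and analysis.**

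| Outcome | Defined in | Scheduled assessment | Analysis named |
|---|---|---|---|
| Time to bony union (primary) | End Points | CT and/or MRI at 1, 12 and 24 months | Descriptive statistics at each time point; no time-to-event method |
| Patient-reported outcomes (primary) | End Points | QOLIBRI and SF-36 are the only patient-reported instruments named: baseline, 1, 12 and 24 months | Descriptive statistics; questionnaire comparison |
| Functional outcomes (secondary) | End Points | QOLIBRI and SF-36, same times | Descriptive statistics; questionnaire comparison |
| Time to weight-bearing, affected limbs | Nowhere | No dedicated assessment in Table 1 | Univariate Cox regression |

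The last row has an analysis but no definition. The first row has a definition and a schedule but no method suited to a time.

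**Step 2. Test whether the limb could be the flap donor leg.** Background says: "Corticoperiosteal tissue from the medial femoral condyle can provide a vascularized source of tissue rich in osteogenic progenitor cells". A donor leg is therefore conceivable. But no donor-limb outcome is an objective or end point, Table 1 has no assessment for one, and a donor site is not naturally called an affected limb.

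**Step 3. See what the schedule allows for time to union.** With planned imaging at 1, 12 and 24 months, an event time is known only to lie in one of four intervals:

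- 0 to 1 month;
- 1 to 12 months (12 − 1 = 11 months wide);
- 12 to 24 months (24 − 12 = 12 months wide);
- beyond 24 months (not united at last look).

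The data are therefore interval-censored. Extra scans done for clinical need may narrow an interval for some patients. If every patient had exactly the three planned looks and union once seen were permanent, the non-parametric estimate would equal the cumulative proportion united at each look. The proportions at 12 and 24 months and the interval-censored estimate thus fit together.

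**Step 4. See what precision 10 patients give for the proportion united.** The exact (Clopper-Pearson) 95% interval for x of n runs from the 0.025 quantile of Beta(x, n − x + 1) to the 0.975 quantile of Beta(x + 1, n − x). With n = 10 and illustrative values of x, which are assumptions:

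| United | Exact 95% CI |
|---|---|
| 5 of 10 | 18.7% to 81.3% |
| 7 of 10 | 34.8% to 93.3% |
| 8 of 10 | 44.4% to 97.5% |
| 9 of 10 | 55.5% to 99.7% |
| 10 of 10 | 69.2% to 100% |

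These intervals are wide, but they describe the primary end point directly and need no data beyond the planned schedule.

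**The case against.** The strongest reply is that the primary outcomes do have a planned analysis. The sentence just before the Cox model promises descriptive statistics for them at each time point. In a single-arm feasibility trial of 10 patients a descriptive primary analysis is legitimate, and the questionnaire comparison can serve the patient-reported primary end point. This stands. A reader might infer that the primary question has no planned estimate at all, and the document does not support that. What is missing is narrower: a method for union as a time.

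Three other stronger readings also fail.

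- A reader might infer that the replacement analysis would be chosen after the data are seen. That cannot be known: a statistical analysis plan may exist and is not shown.
- A reader might infer that Cox regression is invalid because there is one arm. It needs a covariate, not a second arm, and a covariate list may be left to the analysis plan. Low precision with about 10 patients is a fair caution, no more.
- A reader might infer that no participant could have a limb to assess. The article does not list donor sites, and medical review takes place at follow-up visits, so weight-bearing could be noted incidentally.

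One could also argue that weight-bearing is a functional outcome, since the second primary objective concerns function. End Points closes that route by stating that functional outcomes are measured with the two questionnaires.

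None of this rescues the sentence. Nor is the point a detail left to a fuller document: the article states an analysis, and states it for an outcome outside the trial.

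**Conclusion.** Wrong as written. The only named time-to-event analysis addresses an outcome absent from the objectives, end points, schedule of assessments and study population. Time to bony union, a primary end point, is left with generic descriptive statistics and no time-to-event method. The error affects one of three named analyses and one of two primary end points; no sample-size figure or other number in the protocol changes.

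The conclusion rests on the article's text alone and needs no numerical assumption. The intervals shown for the proportion united illustrate what the replacement would deliver and are not part of the proof. The finding does not say that a prespecified union analysis is absent from documents not shown.

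**What to change.** Delete the weight-bearing Cox sentence and bring Analysis into line with End Points:

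- **Union.** Measure bony union from reconstruction (time 0). Report the proportion united at 12 and 24 months with exact 95% confidence intervals, and add a non-parametric time-to-union estimate for interval-censored data, because union is assessed at 1, 12 and 24 months.
- **Denominators.** State the number behind each proportion alongside the existing rule for retrospectively recruited patients with missing or off-window data. The interval-censored estimate can use a scan taken off schedule, such as the article's own example of a 9-month CT.
- **Patient-reported outcomes.** Keep the questionnaire comparison for this primary end point.
- **Covariates.** Label any covariate analysis in about 10 patients as exploratory and descriptive.

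The cost is one paragraph of wording, with no new data and no change to the schedule.

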### Measures for Avoiding and Limiting Bias

The study represents a high-quality clinical study in which bias will be kept to an absolute minimum. The study will be heavily controlled with the well-defined inclusion and exclusion criteria that will ensure that the number of patients with confounding features will be reduced, thereby effectively minimizing sources of selection bias and increasing the homogeneity of the cohort under investigation.

The follow-up period is 24 months. Generally, we would expect to see sufficient bone regeneration for most extensive defects by this time. Ongoing care will be provided in accordance with the recommendations of the treating surgeons and other members with relevant specialties, as appropriate.

### Ethics Approval

The trial will be conducted in accordance with the principles of the Declaration of Helsinki, Notes for Guidance on Good Clinical Practice (CPMP/ICH/135/95), as adopted by the Australian Therapeutic Goods Administration in 2000, and in accordance with the National Health and Medical Research Council’s National Statement on Ethical Conduct in Research Involving Humans [41]. A copy of the signed and dated letter of approval will be provided to the clinical trial site and the sponsor prior to study commencement. Any written information and advertisements that are to be used for subject recruitment will be approved by the Human Research Ethics Committee prior to their use.

It is the responsibility of the investigator to obtain written informed consent from each individual who participates in the study after an adequate explanation (in lay terms) of the aims; methods; objectives; and potential discomforts, risks, and benefits of the study is given. The investigator must also explain to the subjects that they are completely free to refuse to enter the study or withdraw, without prejudice, from the study at any time. Before enrollment into the study, each prospective candidate will be given a full explanation of the study. Individuals who are eligible and wish to participate will be provided the trial’s participant information and consent form (PICF) prior to participation. The PICF details all of the relevant aspects of the trial procedures. Potential participants will be given time to read through the information and ask any questions. The formal consent process will be undertaken by the principal investigator or the associate investigator and will be documented by the trial coordinator. The PICF will be submitted for approval to the Human Research Ethics Committee of the PAH. Participants will be provided with a copy of their signed PICF.

## Results

As of December 2020, we have enrolled 3 participants for the study. We expect to have results before the end of 2023.

## Discussion

### Study Overview

We aim to evaluate the potential of tissue engineering with a bioresorbable, 3D-printed scaffold and autologous vascularized tissue transfer in the reconstruction of acquired calvarial defects. It is essential to undertake a prospective feasibility trial that formally explores this technique to establish its safety and efficacy. This trial will offer critical baseline data against which current and future implants can be compared. Tissue regeneration could be enhanced via scaffold refinements, including additives such as growth factors, osteoprogenitor cells, and vascular networks [35-39]. However, RMAV may always be necessary to optimize tissue regeneration.

The project, as a whole, has a number of benefits for both individuals and society at large. It is expected that the results of our open-label feasibility trial will provide additional evidence on the effectiveness of the RMAV treatment approach for patients with calvarial defects for which contemporary surgical management may have a greater risk of failure or complications [42,43].

### Conclusion

The RMAV technique may be an alternative method of reconstruction for large calvarial defects. It involves performing a vascularized free tissue transfer and using a bioresorbable, 3D-printed scaffold to promote and support bone regeneration (termed the *regenerative matching axial vascularization* technique). This technique may be used to reconstruct skull bone defects that were previously thought to be unreconstructable, reduce the risk of implant-related complications, and achieve consistent outcomes in cranioplasty. This must now be tested in prospective clinical trials.

## Abbreviations

CT: computed tomography
CRF: case report form
MDT: multidisciplinary team
MRI: magnetic resonance imaging
mPCL-TCP: medical-grade polycaprolactone and tricalcium phosphate
PAH: Princess Alexandra Hospital
PCL-TCP: polycaprolactone and tricalcium phosphate
PICF: participant information and consent form
QFAB: Queensland Facility of Advanced Bioinformatics
QOLIBRI: Quality of Life After Brain Injury
REDCap: Research Electronic Data Capture
rhBMP-7: recombinant human bone morphogenic protein-7
RMAV: regenerative matching axial vascularization
SF-36: 36-item Short Form Quality of Life
